#### Methods for additional analyses (e.g. subgroup analyses) {20b}

Subgroups will be divided according to their accompanying diseases, including diabetes mellitus, malignant tumour (or haematologic malignancy), immune insufficiency (human immunodeficiency virus infection or organ transplantation), end-stage renal disease, or comorbidity of more than one of those conditions.

#### Methods in analysis to handle protocol non-adherence and any statistical methods to handle missing data {20c}

Data produced following protocol non-adherence will not be included in the study and will be disclosed. An effort will be made to reduce missing data to a minimum. We will handle missing data with multiple imputations (MICE Package, R ver. 4.0.3, The R Foundation for Statistical Computing, Vienna, Austria). Missing values will be handled appropriately following guidelines [17]

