#### Criteria for discontinuing or modifying allocated interventions {11b}

Patients who do not want to participate in the trial or accidentally lose the PICC within 48 h after the procedure will be excluded from the study. There are no criteria for modifying allocated intervention.

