#### Outcomes {12}

The primary outcome is the effect of subcutaneous tunnelling in PICC placement on the rate of CLABSI. We will use the National Healthcare Safety Network surveillance definition [15]. CLABSI will be defined as a laboratory-confirmed bloodstream infection where the PICC is in place for more than 48 h and must meet both of these criteria: participants have a recognized pathogen identified from one or more blood specimens by culture- or non-culture-based microbiologic test, and organisms identified in the blood are not related to an infection at another origin (e.g. mucosal-barrier injury). A board-certified infection disease specialist will diagnose CLABSI at each institution, independent of this study for blinding.

The secondary outcomes include rates of local infection and bleeding from exit sites, extra procedure time for subcutaneous tunnelling, and technical success, defined as the rate of successful catheter tip placement to the cavoatrial junction. The local infection will be defined as one or combined symptoms followings: insertion site swelling with tenderness, local heating sense, or pus. Bleeding from exit sites will be marked when PICC cannot be kept in place due to continuous bleeding. Minor oozing causing dressing change will not be counted as this outcome. We will divide technical success into two categories. If there is a failure in puncturing the target vein or placing the catheter to the cavoatrial junction, we will define it as ‘impossible PICC.’ In case of subcutaneous tunnelling failure after target vein puncture, we will explain it as ‘impossible tunnelling.’

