### Sample size {14}

According to previous reports about PICC, infection rates range from 0.6 to 7.4% [1, 3–5]. In a previous retrospective study, the CLABSI rate of tPICC was 2.6% [13]. The sample size was calculated by assuming the same infection rate in this trial to verify the prior retrospective study result. In this trial, 2 × 677 participants are needed to prove a reduction of the infection rate from 6.2 to 2.6% for the primary outcome, at a two-sided α level of 0.05 and statistical power of 90%. A total of 1694 participants will be included in this study to account for a 20% dropout rate (PASS, version 16, NCSS statistical software). Data will be analysed on an intention-to-treat basis according to their originally assigned group.

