#### Implementation {16c}

An independent statistician will create the computer-generated block randomization list. Then, each eligible participant with informed consent will be sent to the angiography suite and randomly assigned to a group immediately before the procedure by an independent circulating nurse in the angiography suite.

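### The protocol promises intention-to-treat but also removes randomised patients for early catheter loss and non-adherence; the primary CLABSI comparison could be biased in either direction, by an unknown amount.

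*Protocol article*

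**What the plan says.** Four parts of the protocol article bear on who is analysed.

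- **Sample size {14}:** "Data will be analysed on an intention-to-treat basis according to their originally assigned group".
- **Methods to handle non-adherence and missing data {20c}:** "Data produced following protocol non-adherence will not be included in the study and will be disclosed".
- **Criteria for discontinuing or modifying allocated interventions {11b}:** two groups are excluded. The first is "Patients who do not want to participate in the trial". The second is those who "accidentally lose the PICC within 48 h after the procedure will be excluded from the study".
- **Implementation {16c}:** consenting patients are "randomly assigned to a group immediately before the procedure by an independent circulating nurse".

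Outcomes {12} adds two relevant definitions. The primary event is a "laboratory-confirmed bloodstream infection where the PICC is in place for more than 48 h". Technical success has a failure category that only the tunnelled arm can produce: "In case of subcutaneous tunnelling failure after target vein puncture, we will explain it as ‘impossible tunnelling". The article does not say whether that failure counts as non-adherence. It names no modified intention-to-treat or per-protocol set.

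**The concern.** Intention-to-treat keeps non-adherent patients in the arm to which they were assigned. A rule that leaves their data out cannot hold together with it. A catheter lost after the procedure is always lost after randomisation, and so is any departure from the assigned technique.

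Two things are at stake. First, the groups compared would no longer be the groups that were randomised. If the removed patients differ from the rest in infection risk, and the removals differ by arm, the CLABSI comparison is biased. If failed tunnelling were treated as non-adherence, removal would be one-sided, because the conventional arm has no matching failure. Second, with incompatible rules on paper, the choice of primary analysis set stays open until the results can be seen.

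**Working it through.** **1. The plan's own figure.** Inputs from Sample size {14}: 6.2% versus 2.6%, two-sided α 0.05, power 90%, dropout 20%. With unpooled variance:

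n = (1.960 + 1.282)² × (0.062 × 0.938 + 0.026 × 0.974) / 0.036² = 676.8, so 677 per arm.

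Then 677 / 0.8 = 846.25, so 847 per arm and 1694 in total. Both figures reproduce; the arithmetic is not at fault.

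**2. Timing.** Allocation comes immediately before the procedure ({16c}). Accidental loss within 48 h after the procedure is therefore post-randomisation without exception. The intervention is a single act at insertion ({11c}), so departure from the assigned technique is post-randomisation too. The wording on not wanting to participate gives no time point.

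**3. Effect of one-sided removal with no true effect.** Both arms have a risk of 6.2% and 847 are randomised to each. A share f of the tunnelled arm is removed, and its risk is k times the arm average. Both f and k are assumptions, since the documents give neither.

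Remaining tunnelled risk = 0.062 × (1 − fk) / (1 − f), so the apparent risk ratio is (1 − fk) / (1 − f). Type I error is from the two-sided pooled z test.

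| f | k | Remaining tunnelled risk | Apparent RR | Type I error |
|---|---|---|---|---|
| any | 1 | 6.20% | 1.00 | 5.0% |
| 2% | 2 | 6.07% | 0.98 | 5.1% |
| 2% | 3 | 5.95% | 0.96 | 5.5% |
| 5% | 2 | 5.87% | 0.95 | 5.9% |
| 5% | 3 | 5.55% | 0.90 | 8.7% |
| 10% | 2 | 5.51% | 0.89 | 9.0% |
| 10% | 3 | 4.82% | 0.78 | 22.5% |
| 5% | 0.5 | 6.36% | 1.03 | 5.2% |
| 10% | 0.5 | 6.54% | 1.06 | 6.0% |

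Example for f = 10%, k = 2: 0.062 × 0.8 / 0.9 = 0.0551, a difference of 0.0069. The pooled standard error is 0.01174 and the unpooled one 0.01170. Rejection in favour of tunnelling is Φ((0.0069 − 1.96 × 0.01174) / 0.01170) = 8.4%. Rejection against it is 0.5%. Together they give 9.0% after rounding.

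**4. The rate analysis.** Statistical methods {20a} plans an exact Poisson rate-ratio test. Assuming equal mean dwell in both arms and in the removed patients, that test is conservative at about 4% when nothing is distorted. It rises to about 7% (10% removed, k = 2) and 19% (10% removed, k = 3). The pattern is the same as in the table.

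**5. The 48 h rule alone.** A catheter lost before 48 h cannot carry a primary event. Suppose 5% of the conventional arm is removed for this reason and none of the tunnelled arm. The conventional proportion becomes 0.062 / 0.95 = 6.5%, and the apparent risk ratio is about 0.95. On the rate scale, at most 0.05 × 2 = 0.1 catheter-day per patient is lost. Against an assumed mean dwell of 14 days, that is 0.1 / 14 = 0.7%. The rule therefore hardly moves the rate per catheter-day and matters more for proportions.

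**6. Are the exclusions needed for power?** At the stated rates, the pooled formula gives 95.1% power with all 847 per arm and 89.9% at 677. They are not needed, provided those rates hold among all randomised patients.

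**The case against.** A reader might infer that the exclusions bias the trial towards tunnelling, because failed tunnelling drops out of that arm alone. The documents do not support this. Outcomes {12} places tunnelling failure within the technical-success outcome, so such patients are expected in the data. Nothing calls it non-adherence, and a tunnel attempted without success may well count as adherent. Nothing links difficult tunnelling to infection risk either. One-sided removal is a possible reading only, and the direction is open.

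The size is equally open. Removing 10% at two or three times the average risk implies a CLABSI risk of 12.4% or 18.6% in those patients, against a cited range between reports of 0.6–7.4%. A subgroup could exceed that range, but this is assumed. At 2% removed the effect is negligible.

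Three narrower objections also have weight.

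- The participation wording may partly mean refusal before randomisation, which would be no breach.
- The 48 h rule applies to both arms and concerns patients who cannot have a primary event. It covers accidental loss only, while bleeding that prevents keeping the catheter is an outcome in its own right, so the loss to the safety comparison is limited.
- The non-adherence sentence could mean cutting follow-up at the breach and not deleting the patient. That helps little here: a breach of technique occurs at insertion, so almost no follow-up would remain.

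None of this removes the contradiction between the sample size section and the two exclusion rules.

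**Conclusion.** The point stands as a contradiction that must be resolved. Intention-to-treat by assigned group cannot be followed together with the removal of non-adherent data and of early accidental losses. The same applies to withdrawals, if that wording reaches beyond randomisation. The article states these rules itself, so this is not a detail left to an analysis plan.

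The exclusions can bias the primary CLABSI comparison in either direction. The size cannot be determined from the documents. Under no true effect and assumed one-sided removals of 2% to 10%, the apparent risk ratio runs from 0.78 to 1.06 and type I error from about 5% to about 22%. Equal risk in the removed patients gives no bias. Non-adherence is the main route; the 48 h rule matters mostly for proportions and early-failure outcomes.

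**What to change.** Reconcile sections {11b}, {14} and {20c} as follows.

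- Define the primary analysis set as every randomised patient in the assigned arm, including failed tunnelling and any other non-adherence.
- Count catheters lost within 48 h with their observed catheter-days and no primary event.
- For withdrawals after randomisation, use data up to withdrawal where consent allows. State that refusal before randomisation is a matter of enrolment.
- Keep a set that excludes non-adherence or early loss only as a labelled sensitivity analysis, with non-adherence defined, including whether failed tunnelling counts.

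The cost is mainly wording. The estimate may become slightly less favourable to tunnelling. About 700 patients had been recruited at submission, so data on any already excluded may have to be retrieved.

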#### Plans to give access to the complete protocol, participant-level data, and statistical code {31c}

The entire protocol will be available on the registry website and published here.

### Oversight and monitoring

#### Composition of the coordinating Centre and trial steering committee {5d}

The five authors (one from each institute) take full responsibility for scientific validity, study quality, study conduction, procedures, patient management after AEs, and quality of final study results and reports. All five authors share information through periodic meetings and discuss the study and appropriate management when problems occur.

#### Composition of the data monitoring committee, its role, and reporting structure {21a}

Each monitoring member will hold data monitoring in each institute. During monitoring, a data monitoring committee (DMC) will check whether the source document for the subject is appropriate, confirm that the consent acquisition process and storage are appropriate, review the overall trial performance, conduct an e-CRF review, review the researcher’s binder, collect any AEs from the subject, and follow. In addition, the committee is planning to monitor through verification of safety evaluation and data collection.

Any catheter-related AEs will be checked during the follow-up period and recorded at e-CRF. In case of more than grade II AEs, it will be reported to the principal investigator ([name]) within 24 h. Each DMC member will judge whether the AE is associated with the procedure, and any related AE will be immediately reported to the IRB and principal investigator. Each researcher should report any severe AE (≥ grade III) and any other unexpected problems to the IRB within 15 days.

Three independent members will be appointed to the data and safety monitoring board (DSMB; [name] [Department of Applied Bioengineering, Graduate School of Convergence Science and Technology, Seoul National University, Seoul, Korea], [name] [Department of Radiology, Hanyang University Guri Hospital, Guri-si, Gyeonggi-do, Republic of Korea], [name] [Department of Radiology, Seoul Metropolitan Government-Seoul National University Boramae Medical Center]).

#### Adverse event reporting and harms {22}

AEs will be classified according to the Common Terminology Criteria for Adverse Events (CTCAE) guideline [18]. If more than three minor AEs (< grade III) occur at one site, the investigator of that site will report the AEs to the DSMB. In case of one severe AE (CTCAE III, IV, or V), a DSMB meeting will be held for safety evaluation. In addition, daily checks for each case will be carried out by the research team of each institution and will be communicated with the other research teams.

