#### Interim analyses {21b}

Interim analyses will not be performed.

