## Discussion

This TUNNEL-PICC trial will assess the effectiveness of subcutaneous tunnelling on PICC placement about the CLABSI rate. The results of this study will provide evidence for the application of subcutaneous tunnelling for PICC insertion and help reduce catheter-associated infection.

PICCs have been widely used in contemporary medical practice for their perceived safety, convenience, cost-effectiveness, and versatility. PICC is generally accepted as safe at insertion and relatively free from severe AEs such as CLABSI during the dwelling period [1]. However, recent reports indicated that the incidence of PICC complications is similar to that of standard central venous catheters [5]. This warrants a study adequately designed to verify the effectiveness of an additional subcutaneous tunnelling method over the conventional non-tunnelling method in reducing catheter-related infection.

Techniques and safety regarding subcutaneous tunnelling on PICC were documented by Selby and colleagues [12], but the infection rate in tPICC was not thoroughly evaluated. Kim et al. recently reported that subcutaneous tunnelling could reduce CLABSI in PICC with no significant increase in procedure time [13]. One randomized controlled study regarding tunnelling in patients who had undergone chemotherapy [19]. However, they assessed a relatively small number of participants (*n* = 129) and limited the study population to cancer patients. Thus, a prospective and randomized controlled study is needed to evaluate the effectiveness of subcutaneous tunnelling in PICC. This trial will be the first multicentre randomized controlled research to investigate whether tunnel-PICC insertion reduces catheter-related infection.

There are several limitations of this study. First, although participants and care providers cannot be sure of group allocation, they cannot be blinded. However, the outcome assessor will be blinded. Secondly, this study will be conducted in referral teaching hospitals of various sizes with different characteristics. These can contribute to a heterogeneous cohort but also reflects real-world practice.

This study will be the largest multi-institutional pragmatic randomized controlled trial that can provide guidelines for PICC insertion for patients who are vulnerable to infection.

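### The written DSMB triggers are pooled event counts that the trial's own expected CLABSIs will almost surely set off, so their firing says nothing about the relative safety of tunnelling

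*Protocol article*

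**What the plan says.** Two written rules bring adverse events to the DSMB, both in Adverse event reporting and harms {22}. For severe events: "In case of one severe AE (CTCAE III, IV, or V), a DSMB meeting will be held for safety evaluation". For minor events: "If more than three minor AEs (< grade III) occur at one site, the investigator of that site will report the AEs to the DSMB". Neither rule mentions allocated arm, relatedness, expectedness, patients treated or catheter-days.

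The data monitoring section {21a} sets the scope of recording ("Any catheter-related AEs will be checked during the follow-up period and recorded at e-CRF") and does not exempt the primary endpoint. It uses the same grade III threshold for ethics-board reporting: "Each researcher should report any severe AE (≥ grade III) and any other unexpected problems to the IRB within 15 days". No CTCAE grade is given for CLABSI in either section. The Discussion, however, describes PICCs as "relatively free from severe AEs such as CLABSI during the dwelling period".

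On the expected number of such events, Sample size {14} states that "2 × 677 participants are needed to prove a reduction of the infection rate from 6.2 to 2.6% for the primary outcome", inflated to 1694 in total. It also cites infection rates from 0.6% to 7.4% in earlier reports. Section {21b} states: "Interim analyses will not be performed". Section {23} provides for independent monitoring at every 200 new cases, or every three months if 200 are not reached.

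**The concern.** A trigger informs a safety board if it is more likely to fire when the intervention is harmful than when it is not. Here the trial expects dozens of events of a type that the protocol itself calls severe, and they arise in both arms. Under the planned benefit most of them come from the conventional arm: 6.2/(6.2 + 2.6) = 70%. One event from either arm is enough to convene the board, so the convening does not separate a harmful tunnelling technique from expected background infection. A single CLABSI cannot show whether the tunnel caused it; only a comparison between arms can. Neither written trigger makes or prompts that comparison. The risk is that the board's attention goes to expected endpoint events, while an excess in the tunnelled arm has no written signal of its own.

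**Working it through.** **Inputs.** CLABSI risk 6.2% (conventional) and 2.6% (tunnelled), 677 per arm evaluable, 1694 in total (847 per arm), 20% dropout, and a lowest cited infection rate of 0.6%, all from {14}. Recruitment runs from 16 November 2020 to about June 2023, about 31 months (Trial status). The share *f* of CLABSIs graded III or higher is not in the document. I treat it as an assumption and vary it.

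**The plan's own figure.** The unpooled two-proportion formula at two-sided 0.05 and 90% power gives (1.960 + 1.282)² × (0.062 × 0.938 + 0.026 × 0.974) / 0.036² = 676.8, that is 677 per arm. Then 677/0.8 = 847 per arm, or 1694. The sample size reproduces and is not in dispute.

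**Expected CLABSIs at planned rates.** 677 × (0.062 + 0.026) = 59.6; 847 × 0.088 = 74.5.

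**Probability that the severe-AE trigger fires.** P = 1 − (1 − f·p_C)^n × (1 − f·p_T)^n, with *n* per arm. Other grade III to V events are ignored; they would only raise P.

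Whole trial, n = 847 per arm (the 10% rate in the harm column is an assumption for illustration):

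| Share *f* | Helps (6.2% vs 2.6%) | No effect (6.2% both) | Harm (6.2% vs 10%) | Lowest cited rate (0.6% both) |
|---|---|---|---|---|
| 100% | about 1 | about 1 | about 1 | 0.99996 |
| 25% | about 1 | about 1 | about 1 | 0.92 |
| 10% | 0.9994 | about 1 | about 1 | 0.64 |
| 5% | 0.976 | 0.995 | 0.999 | 0.40 |

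At the planned control rate, the probability barely differs between benefit, no effect and harm. It falls well below certainty only when a rate near the bottom of the cited range is combined with a small severe share.

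**How early it fires.** In the first 200 patients (n = 100 per arm) at planned rates, P is 99.99% at f = 100%, 99% at 50%, 89% at 25% and 59% at 10%.

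**How often it fires.** If each severe event calls its own meeting and every CLABSI is graded severe, 60/31 = 1.9 to 75/31 = 2.4, or about two meetings a month. At f = 10% the same reading gives only 6 to 7 meetings over the whole trial (0.1 × 59.6 to 0.1 × 74.5).

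**Minor-event rule.** At a site with 339 patients, the chance of more than three events is 50%, 91% and 99% at assumed risks of about 1.1%, 2% and 3%. This rule too responds to volume rather than to a difference between arms.

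**The case against.** The strongest reply is that the rule convenes a safety evaluation. It is neither a boundary nor a stopping rule, and a one-event alert is meant to be sensitive, leaving the board to judge once it meets. That stands: the rule does not touch the type I error or bias the primary comparison. It does not rescue the trigger as a signal, because sensitivity to expected endpoint events tells the board nothing that it could not assume beforehand.

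A reader might infer that the plan leaves the board unable to detect harm. The document does not support this. Nothing bars the DSMB from seeing data by arm: the blinding section {17a} covers outcome assessors and data analysts, and {21b} excludes interim analyses without mentioning safety tables. A charter may provide for them. Section {21a} also has each event judged for association with the procedure, and {22} adds daily checks, although these routes are not written as feeding the DSMB.

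A reader might also infer that the trigger is near certain to fire within the first 200 patients, or that the board will meet about twice a month. Both require essentially every CLABSI to be graded III or higher, and the second also requires a per-event reading. CLABSI's severe label is a remark in the Discussion about PICCs in general, not a grading rule, so neither statement can be made unconditionally. Firing at some point in the trial is robust to this at planned rates.

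Finally, the article condenses a longer protocol, and the absence of a by-arm report alone would be no fault. The point rests on what {22} does fix: a trigger that, read with the Discussion, counts expected endpoint events.

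**Conclusion.** The point holds in limited form. The DSMB triggers in {22} are pooled counts without arm or denominator. With 60 to 75 CLABSIs planned, the severe-AE trigger will almost surely fire during the trial under benefit, no effect or harm: 97.6% or more at the planned control rate with 847 per arm, even if only 5% of CLABSIs are grade III or higher. Its firing therefore says nothing about relative safety. This assumes that primary-endpoint events count as adverse events, which {21a} and the Discussion imply and no section denies, and that the trigger applies to both arms, which follows from the absence of any restriction. The weakness lies in safety monitoring; the validity of the final analysis is unaffected. It is worth correcting because the remedy is cheap and, with 700 patients recruited at submission, most of the trial could still benefit.

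**What to change.** 1. In {22}, state how primary-endpoint CLABSIs count towards the single-event meeting trigger, and route them to periodic DSMB review by arm. Leave reporting to the IRB and the principal investigator unchanged.
2. At each monitoring point already set in {23} (200 cases or three months), have the independent statistician give the DSMB a closed table by arm of severe AEs, CLABSI and exit-site events, with patients and catheter-days. State that it is for harm review only, supports no efficacy claim and leaves the final alpha unchanged, so that it sits alongside {21b}.
3. A numerical review threshold is optional and for the DSMB to set. If a one-sided exact comparison at p < 0.025 is used, state its limits. In 20,000 simulated trials with looks every 200 patients up to 1694, it prompted a needless review in about 5 to 6% of trials with no effect. It detected harm in 99% at 6.2% vs 12.4%, 81% at 2.6% vs 5.2%, 38% at 2.6% vs 3.9%, and 25% at 0.6% vs 1.2%. Smaller harms would often be missed, so the threshold should not replace the board's reading of the table.

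Cost: a wording amendment to {22} and {21a} and a short table from data already in the e-CRF. The downside is that the independent statistician and the DSMB see data by arm, with a little extra reporting work.
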